### Objectives

*Primary endpoint*
○ Acute toxicity defined as toxicity occurring during or within 3 months following adjuvant EBRT and scored by:▪ Acute Radiation Therapy Oncology Group (RTOG) small and large intestine toxicity [28] and Common toxicity criteria version 4.0 (CTC v4.0) [29]▪ Acute RTOG [28] and CTC v4.0 [29] bladder toxicity for patients with a neobladder only

*Secondary endpoints*
○ Quality of life (QOL) scoring using the EORTC QLQ-C30 supplemented with QLQ-BLM30 prior to, at the end and 1 month after adjuvant EBRT, then 3-monthly during the first year and 6-monthly up to 2 years.○ Assessment of quality-adjusted-life-years with the EuroQol classification system (EQ-5D) [30]. A written consent to use this system was obtained from the EuroQol Group Foundation.○ Assessment of erectile function using the International Index of Erectile Function (IIEF) questionnaire [31] in males and sexual function in females [32].○ Assessment of voiding pattern using the International prostate Symptom Score (I-PSS) [33] and International Consultation on Incontinence Modular Questionnaire Urinary Incontinence (ICIQ-UI) Short Form [34] for patients with a neobladder.○ Late toxicity due to radiotherapy will be scored using RTOG [28] and CTC v4.0 [29] scoring systems. Late toxicity is defined as toxicity lasting more than 3 months after cessation of adjuvant EBRT, or starting more than 3 months after the end of adjuvant radiotherapy.○ Local control rate defined as absence of recurrence within the pelvis. This will be evaluated on pelvic CT scans performed on predefined time-points (see below) or in case of suspicion of recurrence.○ DFS defined as survival without evidence of disease recurrence (neither local recurrence, recurrence in lymph nodes or distant metastasis) and is calculated from date of radical cystectomy till diagnosis of local, regional or distant recurrence on CT scan at predefined time-points or in case of suspicion of recurrence.○ Bladder cancer specific survival calculated from date of radical cystectomy till death due to MIBC.○ Overall survival calculated from date of radical cystectomy till death of any cause.○ Serum samples and urine samples after cystectomy will be collected and stored in a biobank. Biomarkers will be evaluated on all samples in duplicate and correlated with DFS and bladder cancer specific survival.

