### Inclusion criteria

Eligible patients are patients with M0-MIBC, treated with radical cystectomy and ePLND with ≥1 of the following characteristics:pathological (p)T3-MIBC with presence of lymphovascular invasion on pathological examinationpT4 -MIBC<10 lymph nodes removedpresence of pathological positive lymph nodespositive surgical margins

andWHO performance state 0–2Age ≥ 18 years oldWilling and able to provide a signed informed consent

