### Evaluation and inclusion

A flow chart presenting the different steps from inclusion until treatment is presented in Fig. 1. EBRT should start during week 6–12 after radical cystectomy.

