### Intervention

A ^18^F–FDG-PET-CT is recommended but not obligatory within 4–10 weeks after radical cystectomy to rule out distant metastases.

All patients receive a planning CT on week 5–10 after radical cystectomy. Planning CT is performed in supine position with 3 mm CT slice thickness from the lung top till mid femur.

The target volume comprises the pelvic lymph node areas at risk in all cases. This stems from the observation that most recurrences are in the pelvic sidewall region so that the central pelvis, and the cystectomy bed in particular, might reasonably be spared treatment unless margins are involved [8, 11]. The lymph node regions at risk are the lymph nodes located along the common, internal and external iliac artery, the lymph nodes in the obturator fossa and the presacral nodes. Suspicious lymph nodes on ^18^F–FDG-PET-CT imaging are delineated separately. All delineated lymph node regions at risk are then summed to a structure named as Lnn. The clinical target volume (CTV)_Lnn is then created using an isotropic expansion of 2 mm around the Lnn. The planning target volume (PTV)_Lnn is created using a 5 mm margin around the CTN_Lnn.

The bladder bed is only included in the radiation field if there is a positive surgical margin [8, 14]. Pre cystectomy imaging as well as information obtained from the surgical report and anatomopathological evaluation is used for delineation of the bladder bed.

A median dose of 50 Gy is prescribed to the pelvic lymph nodes ± bladder bed and is delivered in 25 fractions, 5 times a week. A simultaneous integrated boost up to 70 Gy (corresponding to a normalised iso-effective dose of 74 Gy in 2 Gy fractions calculated with an α/β of 10 [35]) to the positive lymph nodes, detected on (^18^F–FDG-PET-)CT, is prescribed. VMAT is used. The treatment is delivered on a linear accelerator using 6–18 MV photons and multileaf collimation [23, 24]. Patient positioning during treatment is controlled by daily cone beam CT.

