### Data analysis

The primary endpoint is acute toxicity defined as any toxicity from start of adjuvant EBRT up to 3 months following adjuvant EBRT.

The incidence of late toxicity will be recorded. Actuarial risk estimates for developing late toxicity will be calculated using Kaplan Meier analysis.

QOL will be evaluated pre-radiotherapy, at the end of radiotherapy and 1 month after radiotherapy. Thereafter a 3 monthly evaluation will be performed during the first year and 6-monthly up to 2 years after radiotherapy.

DFS, bladder cancer specific survival and overall survival will also be calculated using Kaplan Meier actuarial analysis. Survival times are defined from the date of radical cystectomy until an event or last follow up.

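### Survival is counted from cystectomy although patients enter weeks later, so a standard Kaplan-Meier curve modestly overstates overall and cancer-specific survival (and DFS in part)

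*Protocol article*

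**What the plan says.** The time origin is fixed in two sections of the Protocol article. Under Objectives, DFS "is calculated from date of radical cystectomy till diagnosis of local, regional or distant recurrence on CT scan". The other two definitions there read "Bladder cancer specific survival calculated from date of radical cystectomy till death due to MIBC" and "Overall survival calculated from date of radical cystectomy till death of any cause". The Data analysis section names the method, "DFS, bladder cancer specific survival and overall survival will also be calculated using Kaplan Meier actuarial analysis", and repeats the origin for all three: "Survival times are defined from the date of radical cystectomy until an event or last follow up". No delayed entry, landmark or later origin is mentioned.

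Entry comes after surgery. The Inclusion criteria section states: "Eligible patients are patients with M0-MIBC, treated with radical cystectomy and ePLND with ≥1 of the following characteristics". Those characteristics come from the operation and its pathology report. Patients must also consent and be WHO 0-2, and distant metastasis at inclusion excludes them. Under Intervention, PET-CT "is recommended but not obligatory within 4–10 weeks after radical cystectomy to rule out distant metastases". Under Evaluation and inclusion, "EBRT should start during week 6–12 after radical cystectomy".

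**The concern.** A patient who dies after cystectomy but before inclusion never enters the cohort. Nor does one found to have distant metastases in that interval. The weeks between surgery and inclusion are therefore free of these events by design. A standard Kaplan-Meier analysis that puts every patient at risk from the day of surgery counts those weeks as observed survival (immortal time).

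The trial has no control arm, so its survival curves will be read on their own or beside the background figures in the article. The Background hypothesises that adjuvant radiotherapy improves disease-free and overall survival, and the bias runs in that direction. It is systematic, so enrolling more patients would not remove it.

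**Working it through.** **The plan's own figure.** The only design figure is the sample size, which concerns toxicity. With a rate of 25%, a half-width of 10 points and 95% confidence, n = 1.96² × 0.25 × 0.75 / 0.10² = 72.03. Allowing for 5% missing data, 72.03 / 0.95 = 75.8, or 76. It reproduces and does not depend on the survival clock. No design figure is given for survival.

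**Inputs for the bias.**
- 5-year overall survival of 22% for ≥pT3 disease (Background), the lowest overall survival rate cited.
- 5-year cancer-specific survival of 31% (T4) and 48% (T3) (Background).
- Time d from surgery to entry: weeks 6 and 12, the limits of the radiotherapy start window. The inclusion date is not in the shown text, so week 4 is added as an earlier case.
- Assumption: constant hazard.

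**Formula.** If S(t) is survival from surgery and all patients enter at time d, a standard Kaplan-Meier curve from surgery among those who enter estimates S(t)/S(d). The inflation is S(t)/S(d) − S(t).

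**Overall survival.** Hazard h = −ln(0.22)/5 = 0.303 per year. Week 6 is 42/365.25 = 0.115 year, so S(d) = exp(−0.303 × 0.115) = 0.966. Week 12 is 84/365.25 = 0.230 year, so S(d) = 0.933. At 1 year, S = exp(−0.303) = 73.9%; 73.9/0.966 = 76.5% and 73.9/0.933 = 79.2%.

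| | 1 year | 2 years | 5 years |
|---|---|---|---|
| Model survival from surgery | 73.9% | 54.6% | 22.0% |
| Surgery clock, entry week 4 | 75.6% (+1.7) | 55.9% (+1.3) | 22.5% (+0.5) |
| Surgery clock, entry week 6 | 76.5% (+2.6) | 56.5% (+1.9) | 22.8% (+0.8) |
| Surgery clock, entry week 12 | 79.2% (+5.3) | 58.5% (+3.9) | 23.6% (+1.6) |
| Surgery clock, entry uniform over weeks 6-12 (simulated) | 77.8% (+3.9) | 57.5% (+2.9) | 23.1% (+1.1) |
| Clock from entry, same simulation | 73.8% | 54.6% | 21.9% |

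The last row agrees with the first because the hazard is constant in this model.

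**Better survival.** With 50% 5-year overall survival (also cited), entry at week 6 to week 12 inflates by 1.4-2.8 points at 1 year, 1.2-2.5 at 2 years and 0.8-1.6 at 5 years. That is less at the early times and the same at 5 years.

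**Cancer-specific survival**, entry at week 6 to week 12. At 31%: +2.2 to +4.4 points at 1 year and +0.8 to +1.7 at 5 years. At 48%: +1.5 to +3.0 and +0.8 to +1.6.

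**DFS.** The article gives no rate. If 1-year DFS were 50-70% (assumed), and if every DFS event barred entry, the inflation would be 2.9-8.6 points at 1 year and 2.1-4.3 at 2 years. The second condition does not hold, so these are upper bounds under an assumed rate.

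**The case against.** **The origin itself is not an error.** Cystectomy is a usual starting point and is openly stated. It is also compatible with delayed entry, which a full protocol or analysis plan not shown here could specify. This is fair as far as it goes. But the article fixes both origin and method, and a standard analysis run as written gives the biased result.

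**DFS.** A reader might infer that no DFS event of any kind can precede entry. The documents do not support this. DFS counts local and nodal recurrence as events, while the exclusion concerns distant metastasis only. The Abstract lets patients with suspicious nodes on PET-CT enter, and PET-CT is not obligatory, so undetected metastases can enter too.

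**Size.** Week 12 is the latest permitted radiotherapy start, inclusion may be earlier, and 22% is the lowest overall survival cited. At 5 years the inflation is 0.8-1.6 points, against a 95% half-width of 1.96 × √(0.22 × 0.78 / 76) = 9.3 points even without censoring. This stands: the effect is small at 5 years and matters mainly for early estimates.

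**Comparison with surgical series.** A reader might infer a biased comparison with the 22% survival or 30% pelvic recurrence in the Background. The article plans no formal survival comparison and does not say how those series count time. The 30% figure corresponds to local control, for which no time origin is stated. The bias in the trial's own estimates does not depend on these comparisons.

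**Secondary endpoints only.** True. The Discussion gives acceptable toxicity as the aim, and the sample size rests on it.

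**Conclusion.** The point holds in limited form. For overall and cancer-specific survival, the stated origin with a standard Kaplan-Meier analysis is biased upward, and the direction does not depend on any assumed rate. For DFS the same applies only through death, so far as it is counted, and known distant metastasis. Its size cannot be fixed from the documents.

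For overall survival the inflation is about 2.6-5.3 points at 1 year, 1.9-3.9 at 2 years and 0.8-1.6 at 5 years. This assumes a constant hazard from 22% 5-year survival and entry at week 6 to week 12. Earlier inclusion lowers all three figures, and better survival lowers the first two. The real early hazard may be higher or lower than the model's; a higher one, for example from post-operative deaths, would enlarge the bias. The primary endpoint and the sample size are unaffected. The correction is worth making because it is cheap and the bias favours the treatment under study.

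**What to change.** Change the survival definitions under Objectives and the matching sentence under Data analysis in one of two ways:

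- Keep cystectomy as time zero and let each patient join the risk set on the inclusion date (left truncation). The curve is then conditional on survival to the earliest inclusion and should be labelled so. If nearly all patients are included in the same week, the estimate will hardly move and mainly its label changes.
- Count survival times from inclusion or from the first radiotherapy fraction. This is simpler and needs no special risk set. If the first fraction is chosen, the analysis covers patients who start treatment.

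The cost is about one sentence in each section, plus the cystectomy and entry dates for each patient. No extra visits or patients are needed. The survival figures become slightly less favourable, and a later origin makes them less directly comparable with series counted from surgery. Neither option removes selection on performance status and absence of metastasis, so any comparison with such series would still need care.

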## Discussion

For patients with MIBC neo-adjuvant chemotherapy and radical surgery is standard of care [3]. Unfortunately the outcome remains poor for high-risk MIBC patients and the overall survival hasn’t improved significantly over the past years. Further efforts to improve the outcome of these patients are therefore mandatory. Previous trials showed that adjuvant radiotherapy can improve DFS at the cost of severe toxicity [9–20]. The latter limited the enthusiasm to propose adjuvant radiotherapy to patients with high-risk MIBC. In the last decade, major technological advancements in radiotherapy delivery have been realized, resulting in a better coverage of the target volume while sparing more normal tissue (mainly small bowel) and in a more precise delivery of radiation. VMAT is such a technique that can significantly reduce late toxicity [23, 24]. Furthermore, better insights in the pattern of local relapse, based on large surgical data [8–10], enable us to tailor and restrict the radiation field to the area that is at highest risk of developing recurrence. Based on these observations there is a renewed interest in reevaluating the place of adjuvant radiotherapy in those MIBC patients who are at increased risk of developing disease recurrence [36]. The aim of this prospective phase 2 trial is to support the hypothesis that with modern radiotherapy toxicity of adjuvant radiotherapy after radical cystectomy is acceptable.

## Abbreviations

c: Clinical stage
CT: Computed tomography
CTC: Common toxicity criteria
CTV: Clinical target volume
DFS: Disease free survival
EBRT: External beam radiotherapy
EORTC: European Organisation for Research and Treatment of Cancer
ePLND: Extended pelvic lymph node dissection
EQ-5D: EuroQol classification system
Gy: Gray
ICIQ_UI: International Consultation on Incontinence Modular Questionnaire Urinary Incontinence
IIEF: International Index of Erectile Function
IMRT: Intensity-modulated radiotherapy
Lnn: Lymph nodes
MIBC: Muscle invasive bladder cancer
p: Pathological stage
PTV: Planning target volume
QOL: Quality of life
RTOG: Radiation Therapy Oncology Group
VMAT: Volumetric arc therapy
